### Confidentiality {27}

All study-related information and participant information will be stored in locked file cabinets in areas with limited access. All laboratory specimens and data reports will be accessed by a coded ID number. All records that contain names or other personal identifiers will be stored separately from study records. All local databases will be accessed by password. PI will be given access to the cleaned data sets. All data will be password protected. To ensure confidentiality, project team members will be blinded to the data.

### Plans for collection, laboratory evaluation and storage of biological specimens for genetic or molecular analysis in this trial/future use {33}

The total amount of blood collected per patient at each visit was 20ml. Blood samples are collected from peripheral veins and are obtained by standard techniques. They will be tested in laboratory of Shanghai Mental Health Center. The subject’s number and visit number should be pre-labeled on each specimen tube, at which time the researcher will add the patient’s personal information to the label. Biological specimens should be exhausted or disposed after statistical analysis. Storage of biological specimens for genetic or molecular analysis for future use in ancillary studies is not intended.

## Statistical methods

### Statistical methods for primary and secondary outcomes {20a}

Descriptive analysis will consist of means and SD for continuous variables and percentages for categorical variables. Data normality will be tested with the results expressed as mean ± SD or percentage, whenever appropriate. Non-parametric tests will be used if data were not normally distributed. Baseline variables will be compared between the groups using either the Student *t* test or chi-squared test (e.g., sociodemographic data, cognitive function data, biomarkers representing inflammatory mechanisms associated with suicidal ideation and MDD, response and remission rates between groups). To compare primary endpoint, a two-way ANOVA will be used considering group (intervention and sham-control groups) and time points (pre and post-intervention), followed by the Bonferroni post hoc test, in case of significant F ratios. Using a mixed-effects model for repeated measures to analyze change from baseline of BSI scores, time, and their interaction. We will also adopt pretreatment values (e.g., age, gender, baseline BSI, HAMD-17, CRP, and blood cells level) as covariates to correct the possible differences. An intention-to-treat analysis will be conducted, i.e., all participants, regardless of adherence to the intervention, will be included in the final analysis. All calculations will be performed using the R-softawre, and the significance level will be set at *P* ≤ 0.05.

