### Eligibility criteria {10}

#### Inclusion criteria

Ages are from 18 to 50;Meeting the criteria of the Diagnostic and Statistical Manual of Mental Disorder (DSM-5) for current unipolar MDD, which is assessed by at least one professional psychiatrist;Han ethnicity;Right handedness;With a score≥17 on the HAMD-17 [16];With a score≥6 on the BSI [17];Without any pharmacotherapy at baseline or maintaining actual pharmacotherapy for at least 2 weeks before the stimulation initiation and during the total stimulation period.

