### Sample size {14}

The sample size was calculated based on the data from Kalu et al. [22] and Boggio et al. [23]. In these studies, the active tDCS was assumed to be superior to sham tDCS in controlling depression with a conservative mean diference of 0.74 and standard deviation (SD)=25.8. We set the type 1 error, *α* (significance), and the a power at 80%. We used G power software (V.3.1.9.4) to calculate the sample size. The result indicated that a minimum of 30 patients per group are needed (a total of 60 patients). Considering the 20% drop-out rate, 75 patients are needed in our experiment. Finally, we planned to enrol 38 patients per group for a total of 76 included patients.

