## Data collection methods

### Plans for assessment and collection of outcomes {18a}

#### Primary study parameter/endpoint

##### BSI

The primary outcome criterion is the reductive ratio in BSI score after 1 and 2 weeks of the treatment. A treatment response is defined as a 50% reduction in the BSI score and remission is defined as score of 6 in the BSI at any point during the 8-week trial compared with the baseline.

Secondary study parametersMini-International Neuropsychiatric Interview (MINI);HAMD-17, MADRS, and ODQ;YMRS;CGI;SDS;WCST and SCWT;Peripheral venous blood: Biomarkers representing inflammatory mechanisms associated with suicidal ideation and MDD are assessed. (1) Routine tests: The routine tests include calculation of the WBC, CRP, neutrophils, lymphocytes, monocytes, platelets. (2) Specific tests: We collect the peripheral blood serum and store it at −80°C after centrifugation. We examine the NGF, BDNF, GDNF, IL, TNF-α, sTNFr1, sTNFr2. NLR, MLR, and PLR in serum using ELISA.

Data collection will be performed by staff of study who will be trained in how to do assessments. Participants will be familiarized with the equipment and tests of study during screening. For all participants, data collection will be conducted at a certain time, in face-to-face meetings. The peripheral blood collection will be done at the laboratory in Shanghai Mental Health Center.

Participants will receive a SMS text or an email to remind their appointment the day before. PI (YC) of the study will supervise data collection to check the quality, completeness, plausibility, and possible errors of the collected data.

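### Remission is listed among baseline variables and given only an unadjusted test, although it is a fixed BSI cut-off and baseline BSI is already collected

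*Protocol article*

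**What the plan says.** Section {20a} of the protocol article opens its comparative methods with "Baseline variables will be compared between the groups using either the Student *t* test or chi-squared test". The examples in brackets end with "biomarkers representing inflammatory mechanisms associated with suicidal ideation and MDD, response and remission rates between groups". No other between-group test is named for response or remission, and section {20b} says that no further analyses are planned.

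Section {18a}, under BSI, defines both as outcomes after treatment. Response is a halving of the BSI score, and "remission is defined as score of 6 in the BSI at any point during the 8-week trial compared with the baseline". The inclusion criteria require "With a score≥6 on the BSI".

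Later in {20a}, after the ANOVA and the mixed model for BSI change, comes this sentence: "We will also adopt pretreatment values (e.g., age, gender, baseline BSI, HAMD-17, CRP, and blood cells level) as covariates to correct the possible differences". It does not say which analyses it covers.

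**The concern.** A rate that can only be observed after treatment cannot be a baseline variable, so the sentence is misplaced as written. It also fixes a method: a chi-squared test on a two-by-two table takes no covariate.

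That matters more for remission than for response, because remission is an absolute score. With the cut-off read as 6 or below, a patient entering at 6 needs no fall, one entering at 8 needs 8 − 6 = 2 points, and one entering at 25 needs 25 − 6 = 19. Response is relative to the patient's own baseline, so much of this dependence cancels.

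Section {16a} describes no stratification by baseline BSI. With 38 patients per arm, some chance imbalance in starting scores is to be expected. An unadjusted remission comparison carries that imbalance as noise. The sponsor already measures the variable that would remove much of it.

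**Working it through.** **Inputs from the article.** 38 per arm enrolled, 30 per arm evaluable, 20% drop-out, 80% power, effect 0.74 with SD 25.8 ({14}); significance level 0.05 ({20a}; two-sided is assumed); entry BSI of at least 6; remission at a score of 6 ({18a}). **Not given, so assumed:** baseline BSI mean and SD, the correlation between baseline and follow-up BSI, and the remission rates.

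**1. The plan's own figure.** With 0.74 as a standardised difference, n per arm = 2(1.96 + 0.842)²/0.74² = 15.70/0.5476 = 28.7, so 29 by the normal approximation. The noncentral t gives 30 (power 80.5%). Then 60/0.8 = 75, rounded up to 2 × 38 = 76. The plan's figure reproduces. Read literally, 0.74/25.8 would need 19,082 per arm, so 0.74 works only as a standardised difference. No power is stated for remission.

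**2. Score-based simulation, 38 per arm.** 800 trials per setting. Baseline is normal, truncated to 6–38 (upper limit assumed). Follow-up = mean − 5 + ρ(baseline − mean) + noise, less 0.74 SD in the active arm. Remission = follow-up of 6 or below at one visit. Uncorrected chi-squared is compared with a likelihood-ratio test from logistic regression on arm and baseline BSI.

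| Baseline mean (SD) | ρ | Chi-squared | Adjusted | Gain (points) |
|---|---|---|---|---|
| 15 (6) | 0.5 | 71% | 77% | 6 |
| 15 (6) | 0.7 | 77% | 89% | 12 |
| 18 (7) | 0.5 | 68% | 73% | 5 |
| 18 (7) | 0.7 | 70% | 82% | 12 |

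At ρ = 0.3 the gain is 1 to 4 points. For 50% response it is under 2 points. A repeat with 1,500 trials per setting gave about 2 points at ρ = 0.3, 6 to 8 at 0.5 and 12 to 15 at 0.7. The gain also appeared when remission was counted at any of five visits. A wider grid, with the effect set at 0.74 residual SD, gave 1.2 to 15.7 points at 38 per arm and 2.5 to 11.9 at 30 per arm.

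**3. Fixed remission rates, varying prognostic strength.** The chi-squared column is checked by formula. For 20% vs 50% at 38 per arm, z = [0.30√38 − 1.96√(2 × 0.35 × 0.65)]/√(0.16 + 0.25) = (1.849 − 1.322)/0.640 = 0.82, which is a power of 79.5%. Simulation gave 79.3%, against 87.2% adjusted, when the odds ratio per SD of baseline BSI is 3. Gains in points at 38 per arm:

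| Sham vs active | OR/SD 1.5 | 2 | 3 | 4 | 6 |
|---|---|---|---|---|---|
| 20% vs 50% | 1.0 | 3.1 | 7.9 | 9.8 | 12.4 |
| 30% vs 60% | 1.9 | 3.4 | 9.2 | 11.7 | 16.5 |
| 15% vs 45% | 0.9 | 2.5 | 5.9 | 8.8 | 11.3 |
| 30% vs 50% | 2.8 | 6.2 | 9.6 | 13.3 | 15.6 |

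At 30 per arm the largest gain was 17.7 points (30% vs 60%, OR/SD 6). Across everything run, the span is 0.9 to 17.7, or about 1 to 18.

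**4. Is the gain real power?** With no effect, mean 15 and ρ = 0.5, the rejection rates were 5.0% (chi-squared) and 6.0% (adjusted). With 20% remission in both arms at 38 per arm, the adjusted test rejected 0.4 to 1.2 points more often; at 30 per arm, 0.7 to 2.0 points more. With remission near 6% in both arms, its type I error was about 9–10%. So a small part of the gain is test size, and a larger part when remission is rare.

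**The case against.** The strongest case on the other side is that a chi-squared test of a supportive binary outcome is conventional and valid, and that the choice of model is detail for an analysis plan that is not shown. Remission is not among the outcomes listed in section {12}, and the trial was not sized on it. The covariate sentence stands alone and may have been meant to reach remission too. All of this is fair. It lowers the stakes but does not settle the text, because the article does name a test and puts post-treatment rates under a baseline label. If the covariates were meant for remission, the named test cannot use them. If they were not, remission is unadjusted.

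Three stronger readings are tempting, and the article supports none of them.

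- A reader might infer that the unadjusted comparison is biased. Under randomisation, chance imbalance adds variance, and the chi-squared test held about 5% under the null except where remission was very rare, when it was conservative.
- A reader might infer a definite loss, such as 5 to 12 points, because baseline BSI strongly determines remission. The two thresholds make a dependence plausible, but no correlation, BSI distribution or remission rate is given.
- A reader might infer that the protocol firmly fixes an unadjusted analysis. The reach of the covariate sentence is ambiguous, and that is as far as the charge goes.

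The endpoint itself is also loosely worded. The text says a score of 6; the simulations read this as 6 or below, with complete data. A patient entering at 6 already sits at the cut-off, and adjustment does not repair that.

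**Conclusion.** The point holds as a wording defect with a modest efficiency cost. Post-treatment rates sit in the baseline-comparison sentence, and the only test named for remission ignores a covariate that is collected and named elsewhere in the same section.

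The cost in power is about 1 to 18 points under assumed inputs: about 1 to 4 at a baseline-to-follow-up correlation of 0.3, roughly 5 to 8 at 0.5, and 12 to 15 at 0.7. These figures rest on the assumed baseline distributions, effect and prognostic strength, and mostly on remission at a single visit. They include the mild size inflation shown above. Severity is low: the chi-squared test is valid, and the primary BSI analysis and the sample size do not change.

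**What to change.** - Move response and remission out of the sentence on baseline variables, and describe them as post-treatment outcomes.
- Analyse remission by logistic regression on arm and continuous baseline BSI. Report a standardised risk difference with the adjusted odds ratio.
- If remission is rare, use a test that is robust in small samples, such as penalised likelihood or a permutation test.
- Keep the chi-squared test as a sensitivity analysis.
- State which analyses the covariate sentence covers.

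The cost is wording in the analysis plan, best settled before unblinding; no new data, visits or patients are needed. The one small downside is that the odds ratio becomes conditional on baseline BSI, which the standardised risk difference addresses.

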**Methods:**

In this double-blind, randomized, sham-controlled study, 76 MDD patients with suicidal ideation are randomly assigned to either active (*n*=38) or sham (*n*=38) tDCS group. The anode and cathode are placed over the scalp areas corresponding to left and right dorsolateral prefrontal cortex (DLPFC), respectively, and each stimulation lasts for 60 min. The primary outcome is defined as change of Beck Scale for Suicide Ideation (BSI) after 5 and 10 sessions. The change of other clinical assessments, blood biomarkers related to suicidal ideation and depressive sumptoms are defined as secondary outcomes. Blood biomarkers related to suicidal ideation are collected at baseline and after 10 sessions.

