### Additional consent provisions for collection and use of participant data and biological specimens {26b}

On the consent form, the patients can decide to accept being collected plasma to test biomarkers and being contacted in the future regarding the results of the biomarkers. Patients who decline this option still participate in the study.

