### Outcomes {12}

#### Primary outcome

The primary outcome is defined as reductive ratio of BSI after 1 and 2 weeks, as well as, after 5 and 10 sessions.

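### The primary endpoint is a reduction ratio, but its stated test is a pre/post two-way ANOVA that does not fit it, a second model on change is also named, and nothing says which decides

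*Protocol article*

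**What the plan says.** The endpoint is worded in two ways.

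- Abstract, Methods: "The primary outcome is defined as change of Beck Scale for Suicide Ideation (BSI) after 5 and 10 sessions".
- Outcomes {12}: "The primary outcome is defined as reductive ratio of BSI after 1 and 2 weeks, as well as, after 5 and 10 sessions".
- Plans for assessment and collection of outcomes {18a}, under BSI: "The primary outcome criterion is the reductive ratio in BSI score after 1 and 2 weeks of the treatment".

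The section on statistical methods {20a} gives two analyses. The first is "To compare primary endpoint, a two-way ANOVA will be used considering group (intervention and sham-control groups) and time points (pre and post-intervention"; Bonferroni post hoc tests follow if F ratios are significant. The second is "Using a mixed-effects model for repeated measures to analyze change from baseline of BSI scores, time, and their interaction". The section does not say which analysis is primary, which F ratio decides, or whether the ANOVA has a within-patient term. The section on additional analyses {20b} plans none, so neither model is labelled supportive.

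The sample size section {14} gives 30 patients per group for 80% power, raised to 38 per group for dropout.

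**The concern.** Three things do not fit together.

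1. **Endpoint and factor.** A reduction ratio measures the fall from baseline as a share of baseline. Before treatment it is 0 for every patient in both arms, so the pre level of the time factor carries no information. The endpoint has two post-baseline visits, and the factor has one post level without saying which visit that is.
2. **Two models, two scales.** The ANOVA is attached to the primary endpoint (a ratio), the mixed model to change in points. They can disagree, and no rule says which result is the trial's result.
3. **The gate to post hoc testing.** It opens on significant F ratios without naming which. A time effect is expected in both arms, since most patients also receive pharmacotherapy, and it could open the gate with no difference between active and sham.

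At stake are the error rate and power of the one comparison that the trial is built for.

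**Working it through.** **Step 1: the ANOVA on the declared endpoint.** With baseline B and score Y(t), the ratio is (B − Y(t))/B. At baseline it equals (B − B)/B = 0 for all. Run mechanically with n per arm, the two pre cells have zero mean and zero variance. The residual mean square is then s²/2, where s² is the within-arm variance of the post ratio. The group-by-time F is diff² / [(4/n)(s²/2)] = diff² / (2s²/n), and the group F is the same number. This is the square of an ordinary two-sample t statistic at a single post visit, with error degrees of freedom doubled from 2n − 2 to 4n − 4. The second factor adds nothing, and week 1 or week 2 remains unchosen. To be a real two-way analysis, the ANOVA must be run on BSI scores, which are not the declared endpoint.

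**Step 2: the plan's own sample size.** A two-sample t test at two-sided 0.05 (sidedness assumed; {20a} says "the significance level will be set at *P* ≤ 0.05") and a standardized difference of 0.74 needs n = 30 per group, with power 80.5%. Then 60/0.8 = 75, rounded to 76. So 30 per group reproduces as one two-group comparison, with the printed 0.74 read as a standardized difference.

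**Step 3: the ANOVA on BSI scores.** Inputs: n = 30 per group and effect 0.74 from {14}. Assumptions not in the protocol: SD 1 at both times, no baseline difference, bivariate normal scores, pre-post correlation ρ from 0.3 to 0.7.

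- Interaction contrast (difference in changes): true variance 4(1 − ρ)/n.
- Group contrast (difference in pre + post sums): true variance 4(1 + ρ)/n.
- An ANOVA without a patient term uses 4/n for both.

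At ρ = 0.5 and n = 30:

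- *No patient term.* Assumed SE = √(4/30) = 0.365; rejection beyond 1.981 × 0.365 = 0.723.
  - Interaction: true SE = √(4 × 0.5/30) = 0.258. Type I error = 2P(Z > 0.723/0.258 = 2.80) ≈ 0.5%. Power = P(Z > (0.723 − 0.74)/0.258) ≈ 53%.
  - Group: true SE = √(4 × 1.5/30) = 0.447. Type I error = 2P(Z > 1.62) ≈ 10.6%.
- *Repeated-measures fit.*
  - Interaction: noncentrality 0.74/0.258 = 2.87 on 58 df, power about 80%.
  - Group: 0.74/0.447 = 1.65, power 37%.
- *Baseline-adjusted comparison (ANCOVA).* Noncentrality 0.74 × √15/√(1 − 0.25) = 3.31 on 57 df, power 90%.

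Simulation with 20,000 trials per setting agrees with these formulas. For 30 per group:

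| Analysis of BSI scores | Type I error, ρ = 0.3 / 0.5 / 0.7 | Power, ρ = 0.3 / 0.5 / 0.7 |
|---|---|---|
| ANOVA, no patient term, interaction | 2.0 / 0.6 / 0.1% | 53 / 54 / 53% |
| ANOVA, no patient term, group | 8.6 / 10.6 / 13.1% | 52 / 52 / 52% |
| Repeated-measures ANOVA, interaction | 5.1 / 5.0 / 5.2% | 66 / 81 / 95% |
| Repeated-measures ANOVA, group | 5.1 / 4.9 / 4.9% | 42 / 37 / 34% |
| ANCOVA on baseline | 5.1 / 5.2 / 5.0% | 83 / 90 / 97% |

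With all 38 per group, power is 65/67/71% for the interaction without a patient term, 77/89/98% for the repeated-measures interaction, 51/45/41% for the repeated-measures group effect, and 91/96/99% for ANCOVA.

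**The case against.** The strongest reply is that a group-by-time layout with pre and post levels is common shorthand for a repeated-measures ANOVA judged by its interaction, and that the next sentence mentions repeated measures explicitly. On that reading the type I error is correct and power is about the planned 80% at a correlation of 0.5. This stands. A reader might infer from the text that the stated ANOVA has wrong error rates and well under 80% power. The protocol does not support that as a flat statement, because it never says that pairing is ignored. It does not say the opposite either, and it does not name the interaction as the deciding effect.

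Three further inferences are tempting and should not be drawn.

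- **Covariates losing patients.** {20a} says "We will also adopt pretreatment values (e.g., age, gender, baseline BSI, HAMD-17, CRP, and blood cells level) as covariates", and the consent section {26b} says of optional biomarker sampling: "Patients who decline this option still participate in the study". But {20c} plans multiple imputation. {18a} lists CRP and cell counts as routine tests, apart from the stored-serum assays, and the opt-out is not shown to cover them. The covariate list is also only illustrative.
- **A model without a treatment term.** The mixed-model sentence does not name group, but it is loosely worded. The preceding sentence names group, and the objectives and trial design make active against sham the comparison.
- **A fault in percent reduction itself.** Its efficiency against an adjusted score depends on BSI means, SDs and effects that the protocol does not give.

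An analysis plan may settle covariance structure and similar detail. That does not cure a protocol that already fixes two unranked primary analyses on different scales.

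**Conclusion.** The point holds as a mismatch and an unranked choice. The stated test does not fit the stated endpoint, a second analysis on another scale stands beside it, and neither the deciding model nor the deciding F ratio is named.

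The size is conditional. Across the readings that the text allows, with 30 per group, a standardized difference of 0.74 and an assumed correlation of 0.3 to 0.7, the type I error of the deciding test runs from 0.1% to about 13% and power from about 34% to 95%. The favourable reading, a repeated-measures interaction, is valid. It gives up about 17, 9 and 2 points of power against a baseline-adjusted comparison at correlations 0.3, 0.5 and 0.7.

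The mismatch and the missing ranking rest on the text alone. The figures rest on the assumed correlation and on 0.74 being a standardized difference. This should be settled before unblinding, because it determines what counts as the trial's result.

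**What to change.** - Delete the two-way ANOVA, or label it supportive.
- Name one primary analysis: the mixed model for repeated measures on BSI score (or change) at weeks 1 and 2, with group, visit, group-by-visit and baseline BSI.
- Name the active-minus-sham contrast that decides: one week, or both weeks with a stated multiplicity rule. The choice belongs to the investigators, since the objectives name both weeks.
- Use one endpoint wording in the abstract, {12}, {18a} and {20a}, and report percent reduction as secondary.

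**Cost.** This changes the endpoint wording while the trial is enrolling, so it needs a protocol amendment and an entry in the trial registration, as {25} provides. The headline becomes a difference in BSI points instead of a percentage. No new data are needed: the Fig. 1 legend already schedules the primary parameters at baseline and at weeks 1 and 2.
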